### Project implementation process

The results of the literature review and the qualitative and quantitative analysis will be combined to answer the research questions (Fig 2).

**Fig 2 pone.0301732.g002:**
[figure not shown]
HeartGap study design. Fig 2 shows a flow chart of the project implementation process, including a description of the methodology.

### Scoping review

In preparation for the empirical research approach, a scoping literature review will be conducted taking into account the PRISMA-ScR [15]. The objective is to determine the current state of knowledge regarding the implementation of GSC+, by nurses and physicians alike. The literature research will be conducted prospectively over six months. Two researchers screen various databases such as Pubmed, Web of Science, Cinahl using search terms developed specifically for the research question. Possible key words (e.g., implementation, "gender medicine", "gender sensitivity", "gender nursing", cardiology, measure, evidence-based practice) will be combined with Boolean operators. In addition to the systematic search, a snowball system followed by a hand search will be carried out. The search will be limited to German and English publications from 2013–2023. Initially, the abstracts will be screened for eligibility by two independent researchers. Exclusion criteria will be the lack of relevance to the research questions, duplicates and publication in languages other than German or English. After abstract screening, a full-text review will be performed and articles will be included or excluded based on the defined criteria.

### Qualitative data collection and analysis

#### Focus groups

At the outset of the qualitative data collection, a total of 18 focus groups with healthcare professionals in nine pilot hospitals will be conducted. Each focus group will consist of a homogeneous group of cardiologists or nurses (four to six persons per group) from the cardiology or internal medicine department, yielding two sets of interviews per pilot hospital (one with cardiologists and one with nurses). The focus groups will be led by two researchers using semi-structured interview guidelines. Qualitative analysis provides in-depth insights into the perceptions and opinions of the respondents [17]. Therefore, exploratory questions of the following categories will be included in the interviews:

Experiences with GSC+Relevant aspects of GSC+Implementation of GSC+ in the hospitalAcceptance of GSC+ from a medical and nursing perspectiveLevel of implementation of cardiological guidelines and expert standards in practiceFacilitators and barriers to implementing GSC+Measures and recommended actions

As the aim of the study is to develop a strategy for the implementation of GSC+, the updated Consolidated Framework for Implementation Research (CFIR) will be used to consider relevant contextual factors from the outset. The CFIR indicates the complexity of implementation and consists of five domains: innovation, outer setting, inner setting, individuals and implementation process [18]. To achieve successful implementation of GSC+, these domains will be used as the basis for structuring the interview guideline and exploring barriers and facilitators.

Focus group interviews will be recorded, transcribed verbatim and pseudonymized according to ethics standards and scientific rules. The transcripts will be analyzed using MAXQDA software. A qualitative content analysis according to Mayring will be conducted [19]. Based on the transcripts, categories will be formed by deductive and inductive approaches, and new hypotheses may be developed accordingly. The results of the qualitative analysis will be considered in the later quantitative analysis.

#### Expert interviews

To obtain further objective information regarding the implementation of guidelines and expert standards in daily practice, the quality managers of the participating hospitals will also be interviewed. Interviews with care providers and expert interviews with stakeholders in the health care system are also planned. This will provide insight into the status quo and factors influencing GSC+ implementation at the different sites as well as the perception of different professions. The results of the content analysis will contribute to the development of an implementation strategy and appropriate measures and recommended actions from the perspective of health care providers, politics, education, health insurance and science.

### Quantitative data collection and analysis

Following the literature review and qualitative data analysis, questionnaires for quantitative data collection and analysis will be designed for patients and healthcare providers (clinicians and nurses). The aim is to determine the level of gender-sensitive care and to review the respondents’ knowledge and acceptance regarding the content on GSC+ in medical guidelines and expert standards (hypothesis 1). The healthcare provider questionnaire will focus on transfer of medical guidelines and expert standards in routine practice. The patient questionnaire will focus on the patient’s perception of sex and gender in the care process. The aim of the patient survey is to investigate: What needs do patients have with regard to gender-sensitive care and whether their ideas coincide with those of care providers. To collect representative data of professionals and patients, a national roll-out of the study at various hospitals in Germany is planned, and factors such as level of care and location of the hospital and socio demographic factors such as sex and age will be analyzed. The analysis is based on personal characteristics such as sex, age, education and vocational training and migration background.

In order to achieve the highest possible response rate, the survey will be conducted according to Dillman’s Total Design Method [20]. FormPro software will be used to digitize the questionnaire data. Hypotheses will be tested using descriptive and analytical methods (cluster and subgroup analysis). Statistical analysis will be performed using IBM SPSS statistical data analysis software. Validated scales will be analyzed according to the coding manual. Use of the validated Nijmegen Gender Awareness in Medicine Scale (N-GAMS) consisting of three subscales (gender sensitivity, gender stereotypes towards doctors and gender stereotypes towards patients) is also considered [21]. Other validated scales will be evaluated for appropriateness. The questionnaire will be supplemented with specially developed questions and kept as short as possible to achieve a high response rate. Quantitative data analysis will be carried out using the statistical analysis program SPSS, which is suitable for this purpose. The data will be analyzed descriptively and inferentially. Appropriate methods of statistical data analysis will be used. To test the hypotheses, absolute and relative frequencies will be calculated depending on the scale level of the variables (categorical or metric), and appropriate measures of location (arithmetic mean, median, minimum, maximum) and dispersion (standard deviation, interquartile range) will be selected and determined. Inferential statistics will be used to identify correlations. Cluster analyses and subgroup analyses will be used to compare the groups.

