### Hypotheses

The main objectives of the study HeartGap are to investigate the current level of implementation of gender-sensitive care in cardiology, to determine whether there is a discrepancy between existing evidence from guidelines and nursing expert standards and health care practice. Furthermore, the acceptance of GSC+ by clinicians and nurses will be examined. Evidence-based medical guidelines and expert standards are important tools and frameworks for the holistic implementation of medical knowledge and high-quality health care.

The following hypotheses will be evaluated in this study:

The translation of theoretical knowledge about gender-sensitive care (status of guidelines and expert standards) cannot be implemented sufficiently into health care practice due to a knowledge deficit (target state ≠ actual state).The working conditions (staff shortages and budget pressures) are decisive factors for the low level of implementation of gender-sensitive care.There is a lack of sufficient knowledge about the GSC+ requirements formulated in medical guidelines and expert standards.The gender-sensitive care requirements formulated in medical guidelines and expert standards are incompatible with everyday care practice.The gender-sensitive care requirements formulated in medical guidelines and expert standards do not correspond to the attitudes of health care professionals.Aspects such as the age and professional experience of health care professionals and gender as well as the type of hospital and the size of the region can have an influence on the implementation of GSC+.

In summary, the HeartGap study aims to comprehensively assess the situation of GSC+ in cardiology and to investigate the correspondence between existing guidelines, expert standards and actual practice of care. The hypotheses of the study examine potential barriers, including knowledge deficits, working conditions and compatibility problems between the formulated requirements in guidelines and expert standards and daily care routines. In addition, the study recognizes the importance of contextual factors, such as nurse and physician demographics, hospital type and regional size, to the successful implementation of gender-sensitive care. Through this multi-faceted investigation, the study aims to provide valuable insights for better integration of GSC+ into cardiovascular healthcare practice.

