### Setting

The HeartGap study will be conducted prospectively in the German states of Berlin, North Rhine-Westphalia, Lower Saxony, Rhineland-Palatinate. Data will be collected from these states to achieve a representative national sample including eastern and western German states, a city state, large and medium-sized cities, and a rural community. As shown in Table 1 (Attributes (number of inhabitants and grade of care) utilized as parameters to calculate stratified random sample), the study areas will be divided into three categories according to population size (large cities with more than 100,000 inhabitants, cities with 5,000 to 100,000 inhabitants, and rural communities with less than 5,000 inhabitants), and the hospitals will be divided into four categories according to level of care, defined as the number of hospital beds (teaching and research hospital with >800 beds, large hospital with > 800 beds, medium-sized hospital with 501 to 800 beds, and small hospital with ≤500 beds) (Table 1). In Germany, the classification of hospitals into care levels is based on the number of beds, which is why this classification was adopted in the course of the study. Focus groups from each level of care will be conducted in 3 regional categories. Each focus group will consist of either physicians or nurses. In the rural region, focus group interviews will be conducted in a hospital with less than 500 beds due to the lack of larger hospitals.

**Table 1 pone.0301732.t001:** Attributes (number of inhabitants and grade of care) utilized as parameters to calculate stratified random sample.

Level of care -------------------- Population size	Teaching / research hospital with > 800 beds	Hospital with > 800 beds	Hospital with 501–800 beds	Hospital with ≤ 500 beds
Large city (≥ 100,000 inhabitants)				
City (5,000 to 99,000 inhabitants)				
Rural community (< 5,000 inhabitants)	*Hospitals in this stratum do not exist in Germany*	*Hospitals in this stratum do not exist in Germany*	*Hospitals in this stratum do not exist in Germany*	

Table 1 illustrates how the attributes of the number of inhabitants in a region and the nursing degree of a hospital were combined as parameters for the calculation of the stratified sample.

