## Discussion

Patients should receive medical and nursing care according to current guidelines and nursing expert standards. Therefore, this project aims to investigate the extent to which physicians and nurses implement GSC+ in guidelines in routine cardiology practice. This allows to conclude certain aspects about the gender-sensitivity of inpatient care, but additional factors need to be considered. One is the extent to which guidelines are taken into account in health care practice or used as a source of information. In addition, it will be investigated which medical guidelines are already being implemented in routine practice. It is conceivable that health care providers use reference sources other than medical guidelines and nursing expert standards. Health care providers are likely to provide GSC+ intuitively in their daily practice without explicit awareness of gender-sensitive aspects in medical guidelines or nursing expert standards. In addition to analyzing the level of implementation of GSC+, the empirical analysis will assess the gender sensitivity of physicians and nurses. In this context, a focus will be put on whether socio-demographic aspects such as age and gender can have an influence on the degree of implementation of GSC+. It is possible that younger caregivers may exhibit a heightened sensitivity toward GSC+, given the increased prominence of the topic in recent years. Conversely, experienced caregivers who have been in the profession for an extended period might be unconsciously integrating GSC+ into their practice. It may also be possible that the level of care has an influence on the implementation of GSC+, for example, better implementation is conceivable in university hospitals where there is closer proximity to research.

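### Cluster and subgroup analysis are named as the hypothesis tests, but they do not fit the last hypothesis, which combines correlated personal factors with hospital-level factors

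*Protocol article*

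**What the plan says.** In the Protocol article, Quantitative data collection and analysis, the sentence that fixes the method is "Hypotheses will be tested using descriptive and analytical methods (cluster and subgroup analysis". The same section adds frequencies and measures of location and dispersion, also for the purpose of testing the hypotheses. It then states "Inferential statistics will be used to identify correlations" and closes with "Cluster analyses and subgroup analyses will be used to compare the groups". A general clause reads "Appropriate methods of statistical data analysis will be used". No regression, mutual adjustment or hospital term is named.

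The last hypothesis (section Hypotheses) begins "Aspects such as the age and professional experience of health care professionals and gender as well as the type of hospital" and goes on to the size of the region, all as possible influences on implementation. The Abstract makes the influence of age, gender, region and hospital type a focus of the study.

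Table 1 (section Setting) crosses three region sizes with four levels of care. Three of the twelve cells carry the note "Hospitals in this stratum do not exist in Germany", so the rural row has only hospitals with at most 500 beds. The section Recruitment, Quantitative survey, gives 382 clinicians, 386 nurses and 388 patients, nine strata and an average of four hospitals per stratum.

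**The concern.** The last hypothesis asks how several factors act alongside one another, and the methods named for testing it do not estimate that.

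- **Cluster analysis** groups respondents. It gives no estimate or test of an effect stated in advance.
- **Age and experience.** The Discussion considers that "younger caregivers may exhibit a heightened sensitivity toward GSC"+ and, conversely, that "experienced caregivers who have been in the profession for an extended period might be unconsciously integrating GSC+ into their practice". Older staff have generally worked longer, so an unadjusted comparison by age also carries the effect of experience, and the reverse.
- **Region and bed size.** All rural hospitals are small, so an unadjusted rural comparison is partly a comparison of small with larger hospitals.
- **Hospital-level factors.** Type and region are constant within a hospital. The information about them comes from the number of hospitals, not from the number of respondents.

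At stake are a rural effect that is really bed size, an age or experience effect that is masked or misattributed, and hospital-level findings that look firmer than they are.

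**Working it through.** **The plan's own sample size.** Cochran's formula with confidence 0.95 and acceptable difference d = 0.05 (Recruitment), and SD = 0.5 (assumed; none is stated):

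n = 1.96² × 0.25 / 0.05² = 384.15, rounded up to 385.

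The stated 382, 386 and 388 all lie close to this. The figure is the precision of one mean under independent sampling. It contains no hypothesis test and no allowance for hospitals.

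**Hospital-level factors.** Nine strata × four hospitals ≈ 36 hospitals, so m = 382 / 36 = 10.6 clinicians per hospital. The intra-hospital correlation (ICC) is not given; 0.01 to 0.20 is assumed.

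DEFF = 1 + (m − 1) × ICC; true error of a nominal 5% person-level test of a hospital-level factor = 2 × [1 − Φ(1.96 / √DEFF)].

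| ICC | DEFF | Effective n | True error |
|---|---|---|---|
| 0.01 | 1.10 | 349 | 6.1% |
| 0.05 | 1.48 | 258 | 10.7% |
| 0.10 | 1.96 | 195 | 16.2% |
| 0.20 | 2.92 | 131 | 25.2% |

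Results for 386 nurses are the same to within 0.1 percentage points. A simulation with 36 hospitals × 11 respondents, 18 hospitals per side, gave 11.3% at ICC 0.05 and 17.2% at ICC 0.10 for the person-level test. The same comparison on hospital means gave 5.3% and 5.2%.

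**Region and bed size.** Take the nine existing cells, equally weighted, with a true effect of +0.3 SD for hospitals with at most 500 beds and no region effect (assumed). Unadjusted means:

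- large city: (0 + 0 + 0 + 0.3) / 4 = 0.075
- city: 0.075
- rural: 0.300

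The spurious rural excess is 0.300 − 0.075 = 0.225 SD. In general it is (1 − w) × effect, where w is the share of the comparison group in hospitals with at most 500 beds; here w = 0.25. The stratum weights are not shown. With w = 0.75 the excess would be 0.25 × 0.3 = 0.075 SD.

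An additive model (intercept, two region terms, three level-of-care terms) has rank 6 of 6 over the nine cells. It returns 0 for rural and 0.3 for at most 500 beds. The full interaction has 12 parameters but rank 9, so it cannot be estimated.

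**Age and experience.** The correlation r is not given. The variance inflation in a joint model is 1 / (1 − r²): 2.0 at r = 0.7, 2.8 at 0.8, 5.3 at 0.9. The two effects can be separated, but only jointly and with lost precision.

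**Could cross-classified subgroups do it instead?** 382 / 9 = 42 clinicians per cell. Splitting each cell in two by age, experience and gender leaves 42 / 8 ≈ 5.

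**The case against.** The section does not say that subgroups are taken one factor at a time, and "Appropriate methods of statistical data analysis will be used" and "Inferential statistics will be used to identify correlations" leave room for regression or a mixed model. Model form and covariates often sit in an analysis plan, which is not shown. The main research question is descriptive, and descriptive measures suit it. All of this is fair. It does not correct the sentence that names the tests: an analysis plan would have to override that sentence rather than fill it in.

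Several stronger readings are tempting, and the documents do not support them.

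- **That hospital-level factors will be analysed as if they varied by person.** No unit of analysis is stated.
- **That the design entangles age with experience.** They are correlated by nature. Region and size are entangled only through the rural row; large city and city are crossed with all four levels of care.
- **That experience has been left out.** The list of personal characteristics is introduced as examples, the hypothesis names experience, and the questionnaires were still to be designed.
- **That clusters will be compared on the variables that built them.** Nothing says so.
- **That age and experience effects will cancel.** The Discussion speaks only of possibilities, and of sensitivity in one case and practice in the other. Placing both on one outcome with effects of −0.3 and +0.3 SD and r = 0.85 gives a marginal age slope of −0.3 + 0.85 × 0.3 = −0.045 and about 14% power at n = 382. With −0.3 and +0.1 the slope is −0.215 and power about 99%. The result depends on the chosen effects.

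**Conclusion.** The point holds in a limited form. The plan states a method for testing its hypotheses that is ill-suited to the last one: cluster analysis does not test a stated effect, and unadjusted subgroup comparisons do not separate the factors that the hypothesis lists together. This is a poorly fixed method, not merely missing detail.

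The sizes are conditional. The false rural effect is three quarters of any bed-size effect with equal cells, and less if the comparison group is weighted towards small hospitals. The error of 6% to 25% applies only if hospital is ignored, and rests on about 36 hospitals and an assumed ICC of 0.01 to 0.20. It is a risk that the wording leaves open, not something the plan says it will do. No firm figure can be put on the loss for age and experience.

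**What to change.** For the last hypothesis, replace the cluster and subgroup wording with one pre-specified multivariable model per profession (clinicians, nurses):

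- **Outcome:** implementation of gender-sensitive care.
- **Factors:** age, years of experience, gender, level of care and region size. Level of care and region enter additively, because their full interaction cannot be estimated.
- **Hospital:** a random intercept or cluster term.

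Make sure the questionnaire records years of experience. Analyse knowledge, workload and attitude in separate models with the same hospital term. They may mediate the effects of the other factors, and including them in the same model would change what those coefficients mean. Keep cluster analysis as an exploratory typology.

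The cost is analysis wording and, if it is not already planned, one questionnaire item; SPSS, the planned software, can fit such models. The real price is wider intervals for hospital-level factors. The rural contrast suffers most: within hospitals of at most 500 beds it rests on one rural stratum against two others, about 4 versus 8 hospitals, and should be reported with that limitation.

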### Ethics approval and informed consent

The study is considered "uncritical" and has been approved by the local ethics committee of the Hannover Medical School in Hannover, Germany (approval number 1075_BO_K_2023). This ethics vote is presented to all hospitals prior to data collection. They have the option of agreeing to it or conducting their own ethics vote. The questionnaires for clinicians, nurses and patients are submitted separately to the ethics committee of Hannover Medical School before the quantitative analysis. Written informed consent will be obtained from all participants prior to enrollment. All participants will receive concise and clear information about the scope and nature of the study and how their personal data will be processed and used. Participants will be informed of their right to withdraw at any time without consequence. The study will be conducted in accordance with the principles of the Declaration of Helsinki.

## Discussion

Patients should receive medical and nursing care according to current guidelines and nursing expert standards. Therefore, this project aims to investigate the extent to which physicians and nurses implement GSC+ in guidelines in routine cardiology practice. This allows to conclude certain aspects about the gender-sensitivity of inpatient care, but additional factors need to be considered. One is the extent to which guidelines are taken into account in health care practice or used as a source of information. In addition, it will be investigated which medical guidelines are already being implemented in routine practice. It is conceivable that health care providers use reference sources other than medical guidelines and nursing expert standards. Health care providers are likely to provide GSC+ intuitively in their daily practice without explicit awareness of gender-sensitive aspects in medical guidelines or nursing expert standards. In addition to analyzing the level of implementation of GSC+, the empirical analysis will assess the gender sensitivity of physicians and nurses. In this context, a focus will be put on whether socio-demographic aspects such as age and gender can have an influence on the degree of implementation of GSC+. It is possible that younger caregivers may exhibit a heightened sensitivity toward GSC+, given the increased prominence of the topic in recent years. Conversely, experienced caregivers who have been in the profession for an extended period might be unconsciously integrating GSC+ into their practice. It may also be possible that the level of care has an influence on the implementation of GSC+, for example, better implementation is conceivable in university hospitals where there is closer proximity to research.

Another important factor is the extent to which medical guidelines and nursing reflect the current state of knowledge and evidence. As authors of medical guidelines and nursing expert standards are not obligated to include gender-sensitive aspects, their inclusion in guidelines is largely dependent on the interests of the guideline authors. In addition, guidelines often do not reflect the current state of medical evidence and it may take several years for the current state of knowledge to be reflected in the guidelines. In particular, nursing expert standards generally do not include comprehensive GSC+ provisions and tend to contain limited information on GSC+. Therefore, it may be worthwhile to include evidence from further studies on gender-sensitive care in our study.

Cardiological Guidelines and nursing expert standards contain gender-sensitive treatment of men and women but do not consider specific transgender and non-binary needs. Due to the limited number of transgender and non-binary individuals included in CVD studies, evidence-based recommendations for the gender-sensitive treatment of these individuals are lacking in medical guidelines and nursing expert standards. However, transgender and non-binary specific needs will be considered in the empirical approach of our study and if evidence in literature regarding the GSC+ of transgender and non-binary individuals is identified it may be included in our study as well.

The successful implementation of GSC+ requires a multidisciplinary approach in which different actors collaborate. Several interdependent dimensions must be considered when examining strategies to promote the implementation of GSC+. It should be given a special consideration to health policy when examining the question of GSC+ implementation, since health policy provides the framework for the implementation of GSC+ in health care practice. The results of this health care research study could contribute to the development of GSC+ policy recommendations. Currently, the state of our national gender health policy is certainly less advanced than at the international level, e.g. Canadian research institutes are leaders in gender health research (CIHR). Given the importance of GSC+ and the research deficits in Germany in this area, it is important for German policymakers to support GSC+ research in order to promote the generation of GSC+ knowledge and evidence in this specific context.

